### Study Population

The study population comprises families or caregivers with boys aged between 5 and 15 years who were genetically diagnosed with DMD and are seeking consultation at the pediatric neurology clinic of the government tertiary care center. Caregivers defined as the persons who look after the patients in the hospital or at home (parents or family members). This excludes hospital staff and paid workers hired by the family.

### Selection Criteria

Boys with DMD presenting to the Pediatric Neurology Clinic were screened for enrollment in the study. The selection of participants was carried out by a pediatric neurologist. Those who fulfilled the inclusion and exclusion criteria were included in the study after providing informed consent. Textbox 1 lists the inclusion and exclusion criteria for this study.

Inclusion and exclusion criteria for this study.
**Inclusion criteria**
Families with boys aged 5 between 15 years who have Duchenne muscular dystrophy (DMD) or Becker muscular dystrophy (BMD) and display clinical symptoms and creatine kinase (CK) levels elevated 10 times or more the normal levelLaboratory genetic confirmation of DMD or BMD by multiplex ligation-dependent probe amplification (MLPA), polymerase chain reaction (PCR), next-generation sequencing (NGS), or muscle biopsy (showing absence of dystrophin expression on immunohistochemistry)Caregivers of the patients with who have access to a smartphone and internet connection
**Exclusion criteria**
Caregivers and patients who are unwilling to participate or unable to comply with the study protocol and visitsCaregivers and patients who did not provide consent to participate

### Intervention Program

#### Routine Care

Boys with clinical symptoms suggestive of DMD were first consulted and evaluated in the pediatric neurology clinic. After detail clinical investigations, a treatment plan for the patient was decided as per the institutional protocol for the management of muscular dystrophies and discussed with the patient. The patient was required to visit the health facility routinely once every 3 months. For multispecialty care, patients visited different subspecialists as required. Physiotherapy and orthosis appointments, along with visits to specialty care units, increase hospital visits, often leading to confusion, treatment nonadherence, and loss to follow-up. The components of routine management are given in Textbox 2.

The components of routine management as per institutional protocol (standard operating care).Confirm diagnosis: clinical examination, investigations, confirmation of diagnosis with genetics, and muscle biopsyFamily counselingBaseline assessment of motor attributes with the 6-Minute Walk Distance Test, Time Function Test, and Vignos and Brooke scalesBaseline cardiac, respiratory assessment, spine, bone health, and endocrine evaluationOral supplementals of calcium and vitamin DNighttime ankle-foot orthosisPhysical therapy muscles strengthening and stretches to reduce contracturesVaccination (immunization)Steroids as per standard guidelinesDietary adviceAdvice on play and leisureThree monthly clinical check-ups for disease progression, monitoring for weight, height, blood pressure, ophthalmic evaluation, bone health, and steroid side effects (these visits may be more as per disease progression requirement).Prenatal diagnosis, carrier screening, and genetic counseling

#### PCC: Comprehensive DMD-Telecare Model

The rationale behind developing the PCC model for patients with DMD was to (1) provide basic information to the patient and their parents or caregivers so that they can effectively understand the disease and participate in the process of obtaining comprehensive care in a resource-limited setting and (2) create awareness about the importance of managing the disease not only pharmacologically but also by improving QoL.

After a systematic review of literature, the intervention designed was based on the Theory of Planned Behavior and tailored to each stage of the study [36]. The conceptual model of PCC is given in Figure 2. The telecare component was added to the model considering the challenges that patients and their caregivers experience when having to travel to the heath care facility frequently, especially in low- and middle-income countries (LMICs). The components of the intervention are provided in Table 1.

The purpose of the intervention is to reduce the number of in-person visits the patient has to make to the clinic. The planned physical follow-up to the health facility during phase 2 is at 6 months. Families are called for physical follow-up only if indicated and instructed by the clinician within 6 months. These visits are recorded.

Protocol material for the Comprehensive DMD-Telecare Model is circulated among pediatricians and pediatric physiotherapists working at the Pediatric Neurology Clinic, School of Public Health experts at PGIMER, and caregivers or parents.

A preliminary version of this package was circulated among specialists for consensus validation and modified according to the feedback received. Thereafter, it was pilot tested among 5 patients and their caregivers. Further corrections were made as needed. Textbox 3 lists the outcomes of the study.

**Figure 2 figure2:**
[figure not shown]
Overview of patient-centered care (PCC): intervention model. DMD: Duchenne muscular dystrophy; PPT: PowerPoint presentation.

**Table 1 table1:** Components of the intervention.

Component	Description
Informational session about the disease	Information sessions are carried out via PowerPoint presentation, and a “Care Guide Companion” booklet is provided (both hard copy and digital). The booklet is designed to helping patients and their caregivers participate in decision-making for their treatment. The components of the booklet include (1) basic information related to DMD^a^, (2) management of DMD, (3) role of the care provider team, and (4) support groups to help people living with DMD.
Instructions and checklist	Instructions are given to the patients and their caregivers to make them understand all the activities that will be carried out once they enter phase 2 of the study. Audiovisual media and images containing instructions for stretches or physiotherapy and physical activity are provided to the family.
Compliance diary	The patient is expected to comply with the prescribed procedures and medications. A customized daily planner is introduced to each patient in phase 2 to increase their adherence to the protocol. This contains periodic monitoring of weight, height, blood pressure, daily medication (eg, steroids, ACE^b^ inhibitors, calcium, and vitamin D), and daily exercise routine. Some clinical evaluations are expected to be performed at home (eg, Gower sign, Vignos score, Brookes scores, etc) which are monitored by the research team over the phone.
Teleconsultation	A total of 3 monthly video teleconsultations are given to the patients by clinicians to provide diagnostic or therapeutic advice electronically. The patient does not have to visit the clinic in person. This is done through: (1) review videos that the family shares with the care team regarding the patient’s present state of illness. These videos are recordings of physical activities that the patient can perform at home, which are share with the team for evaluation purposes; and (2) customized videos: As per the clinical requirements, customized videos are shared with patients to address any additional needs.
Multidisciplinary teleconsultation	Not all subspecialists are needed at all ages or stages, but they must be accessible if necessary.

^a^DMD: Duchenne muscular dystrophy.

^b^ACE: Angiotensin-converting enzyme.

Study outcomes.
**Primary outcomes**
Difference in quality of life (QoL) with and without the interventionDifference in out-of-pocket (OOP) expenses incurred by patients and their caregivers with and without the interventionDevelopment of patient-centered care (PCC) model known as the Comprehensive Duchenne muscular dystrophy (DMD)-Telecare Model

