Accordingly, this study aims to estimate the economic burden incurred by the families of children with DMD seeking care at a government hospital. Next, we aim to develop a PCC model (intervention) to build the capacity of affected families to cope with DMD, thus reducing the financial burden on families. Finally, we aim to compare the impact of intervention with routine care on QoL (caregiver and patient) and economic burden after 6 months of intervention.

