### Setting and Sample Size Considerations

Patients were recruited prospectively in a consecutive manner from the Pediatric Neurology Clinic of the Advanced Pediatric Center at PGIMER in Chandigarh, India. This institute caters to approximately 7 north Indian states, namely, Punjab, Haryana, Himachal Pradesh, Jammu and Kashmir, Uttarakhand, Bihar, the northwestern part of Uttar Pradesh, and the Union Territory of Chandigarh.

The sample size estimation for the primary outcome was in accordance to changes in patients’ health-related QoL (HRQOL) questionnaire scores. The QoL scores were assessed in the observational phase (0-6 months) and compared with the QoL scores in the intervention phase (7-12 months). A clinical meaningful difference based on the minimum important difference from HRQOL was 0.1 [34], along with an SD of 0.2 [35] and an allocation ratio of 1:1. The estimated sample for the study was 126 (63 patient in each phase) to achieve a level of significance of 95% CI at a power of 80%, accounting for a 10% dropout rate. The total sample size was 140, with 70 patients in each phase.

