**Primary outcome measures**
Change in QoL mean scores in phase 1 (0-6 months) and phase 2 (7-12 months) of the studyChange in mean OOP expenses incurred by the patients and their caregivers with and without the intervention

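### The sample size rests on one primary outcome (the child's HRQOL), but the outcome list makes both an unspecified QoL score and OOP expenses primary, with no stated rule linking the two

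*Protocol article*

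**What the plan says.** In Setting and Sample Size Considerations the primary outcome is singular: "The sample size estimation for the primary outcome was in accordance to changes in" patients' HRQOL scores. The inputs are specific to that outcome: "A clinical meaningful difference based on the minimum important difference from HRQOL was 0.1", an SD of 0.2, "and an allocation ratio of 1:1", and a sample "to achieve a level of significance of 95% CI at a power of 80" percent, "accounting for a 10% dropout rate". The result is 63 per phase (126), raised to 70 per phase (140).

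Textbox 3, under Primary outcomes, lists three items: a difference in QoL, a difference in "out-of-pocket (OOP) expenses incurred by patients and their caregivers with and without" the intervention, and development of the Comprehensive DMD-Telecare Model. Under Primary outcome measures there are only two: "Change in QoL mean scores in phase 1 (0-6 months) and phase 2 (7-12 months"), and the change in mean OOP expenses. The third item has no measure.

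Textbox 3 does not say whose QoL is meant or which score. The aims at the end of Economic Burden of Disease are to "compare the impact of intervention with routine care on QoL (caregiver and patient) and economic burden after 6 months of intervention". Data Management and Analysis describes an EQ-5D-5L index and an EQ VAS for the child, and four WHOQOL-BREF domain scores for the caregiver. It says that comparative analyses will be done and names tests. It does not rank the primary outcomes or say whether one or all must succeed.

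**The concern.** A study sized on one primary outcome and reported on a list of primary outcomes has two different success criteria. The stated 5% level and 80% power belong to one comparison. Once OOP is also primary, the error rate of the primary claim depends on a rule that the article does not give. If either result may carry the claim, the false-positive rate exceeds 5%. If both must succeed, the error rate does not rise, but joint power is below the power for HRQOL alone. Leaving the QoL score open adds a further choice that could be made after the results are seen.

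This goes beyond detail that an article leaves to an analysis plan. An unseen plan could supply an adjustment, but the sample-size section and Textbox 3 would still disagree on how many primary outcomes there are.

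**Working it through.** **1. The protocol's own figure.** Inputs from Setting and Sample Size Considerations: difference 0.1, SD 0.2, 1:1, 95% level (taken as two-sided 5%), 80% power.

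n per phase = 2 × SD² × (z₀.₉₇₅ + z₀.₈₀)² / difference² = 2 × 0.04 × (1.960 + 0.842)² / 0.01 = 62.8, so 63. With 10% dropout: 63 / 0.9 = 70 per phase, 140 in total. Both stated figures reproduce, for one two-sided 5% test. A one-sided test would give 50, which does not match.

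**2. Number of primary comparisons.**
- Narrow reading: one QoL score plus OOP, which is 2.
- Widest reading: EQ-5D-5L index, EQ VAS, four WHOQOL-BREF domains and OOP, which is 7.
- Development of the care model adds none, because it has no measure and no test.

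**3. Chance of at least one false positive, if each test is at 5% and any one may carry the claim.** Under independence this is 1 − 0.95^k. The correlations in the table are assumptions, since the article gives none; those rows were simulated with equally correlated two-sided z-tests.

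| Correlation | 2 tests | 7 tests |
|---|---|---|
| 0 | 9.75% | 30.2% |
| 0.5 | 9.1% | 23.0% |
| 0.7 | 8.4% | 17.9% |

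**4. Effect of controlling error across two primaries.** Holm compares the smaller p-value with 0.05 / 2 = 0.025 and, if that is significant, the larger with 0.05.

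With 63 per phase on the unpaired formula, the standardised effect is 0.1 / (0.2 × √(2/63)) = 2.806.
- Power at 0.05: Φ(2.806 − 1.960) = 80.1%.
- Power at 0.025: Φ(2.806 − 2.241) = 71.4%.

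The 71.4% is a floor under Holm. HRQOL is tested at 0.05 whenever OOP has already passed at 0.025.

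Restoring 80% at 0.025 on the same formula needs 2 × 0.04 × (2.241 + 0.842)² / 0.01 = 76.04, so 77 per phase, or 77 / 0.9, so 86 with dropout.

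**5. Paired analysis.** The same children are measured in both phases, and a paired *t* test is among the tests named. With within-child correlation r (an assumption), the SD of the change is 0.2 × √(2(1 − r)). For 63 children at 0.025, the normal approximation gives:
- r = 0: 71.4%.
- r = 0.3: SD of change 0.237, Φ(3.354 − 2.241) = 86.7%.
- r = 0.5: SD of change 0.200, Φ(3.969 − 2.241) = 95.8%.

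**The case against.** The strongest reply is that the inflation is inferred from silence. The article states no rule that any single positive result suffices, and it sets no significance level for OOP or caregiver QoL. Decision rules and multiplicity control are often left to the analysis plan. This stands: the error figures are conditional on the rule, and the article cannot be said to permit a claim on any one score.

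A reader might also infer seven primary tests and a 30% error rate. The document does not support that as its plain meaning. The QoL measure in Textbox 3 uses the same phase windows as the sample-size section, where they refer to patients' HRQOL. A difference of 0.1 with an SD of 0.2 fits a utility index. Nothing makes the EQ VAS or each WHOQOL-BREF domain a separate primary test. The aims do include caregiver QoL, so the wide reading remains possible, but only as an upper bound.

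Two further inferences fail. Listing model development as an outcome is a labelling fault and cannot produce a chance positive. The article also does not claim 80% power for OOP or caregiver QoL; it ties that figure to patient HRQOL.

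It is also fair to say that economic burden is central to the title and aims, so OOP need not be demoted. And in an uncontrolled before-after study, whose own limitations note that conditions may differ over time, multiplicity is not the largest threat. Neither point removes the disagreement between the two sections.

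**Conclusion.** The point holds as a contradiction in the current text. The sample size assumes one primary outcome, patient HRQOL. Textbox 3 has two measurable primary outcomes, one of them with neither person nor score named, plus a deliverable that is not an outcome.

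The sample-size arithmetic is correct for its own inputs. The fault lies in the definition of the primary outcome. Its size is a family-wise error of up to 9.75% instead of 5%, assuming two independent tests, each at 5%, with either allowed to carry the claim. The 30% figure applies only on the widest count of QoL scores.

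This should be corrected, and there was still time at publication: Results says that the data were being entered and cleaned, with no impact data available.

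**What to change.** Reconcile Setting and Sample Size Considerations with Textbox 3 before impact data are analysed:

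- Name the child's EQ-5D-5L index as the primary QoL score.
- Keep OOP expenses as the second primary outcome, with Holm across the two. If the investigators prefer the single primary outcome of the sample-size section, test OOP at 5% only after a significant QoL result.
- Report the EQ VAS and the four WHOQOL-BREF domains as secondary, with estimates and confidence intervals.
- List development of the care model as an objective and not as an outcome.

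The cost is mostly wording. Under Holm, HRQOL may have to pass at 0.025, where power on the unpaired formula at 63 per phase is about 71% and not 80%. A paired analysis with positive within-child correlation recovers some or all of that. Under the ordered alternative HRQOL keeps its 5% level and stated sample size, but OOP can be claimed formally only if QoL succeeds. Phase 2 had already ended, so the change must be dated and documented as made after data collection and before analysis.

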**Primary outcome measures**
Change in QoL mean scores in phase 1 (0-6 months) and phase 2 (7-12 months) of the studyChange in mean OOP expenses incurred by the patients and their caregivers with and without the intervention
**Secondary outcomes**
Socioeconomic determinants of primary outcomes.Feasibility of follow-up via telephonePattern of health care utilization for different stages of DMDNeuromuscular QoL in the pediatric age groupOpinions and experiences related to the challenges faced by stakeholders during the management of DMD (noted verbatim)
**Secondary outcome measures**
Demographic data and socioeconomic status in terms of means and percentagesCompliance with telephone follow-up and satisfaction index on Likert scaleMean score of neuromuscular QoL in the pediatric age groupThematic analysis of the qualitative data

### Data Collection

At the time of recruitment, primary caregivers are interviewed on their social and demographic characteristics and QoL. Further, after the initiation of phase 1, these caregivers are contacted again prospectively to assess the economic burdens they face by collecting data on out-of-pocket (OOP) expenses incurred during the treatment of DMD. The data on economic burden include information on household consumption expenditure, patient-level expenses incurred on diagnosis and treatment related to DMD, and coping mechanisms for dealing with DMD. A pretested semistructured schedule, adapted from previous studies in similar settings, is used to interview the patients [37-39]. Cost-of-illness (COI) analysis is carried out to assess OOP expenses, which are further classified as direct and indirect expenses [40]. Expenditure on the diagnosis, drugs or consumables, hospitalization, user fee, or procedure fee is considered direct health care expenditure. Transportation, boarding, loading, and food are taken as direct non–health care expenditures. Wage or income loss by the accompanying caregivers during the period of treatment is considered an indirect expenditure.

Information on economic burden is gathered from the caregivers throughout the follow-up period of 12 months. Data are collected during their physical visits as well as telephonically every month.

HRQOL of the patients and their caregivers are gathered at the baseline and then at the completion of phases 1 and 2. QoL of caregivers is also recorded at the 3 data points (baseline, end of phase 1, and end of phase 2). The study design is further explained in Figure 1.

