## Methods

### Study Design

This is a longitudinal quasi-experimental study that will be conducted in 2 phases. It is important to note that within the scope of this study, it is difficult to achieve a controlled experimental design. There is no randomization, and the same group of subjects are to be compared before and after the intervention. The experimental condition may be systematically different across the time frame. Considering this limitation, we chose a quasi-experimental design for this study. [33]

Phase 1 of the study is observational, and no intervention is administered. Participants (previously diagnosed and under follow-up as well as new patients) were recruited prospectively from pediatric neurology clinic, department of Pediatrics, Advanced Pediatrics Center, Post Graduate Institute of Medical Education & Research (PGIMER), Chandigarh, India. Detailed information about the study was provided to the children and their caregivers. After providing consent to participate in the study, the primary caregivers were interviewed for demographic information, clinical information, and information related to their economic status and financial burden of disease caused by DMD. The QoL of patients and caregivers was assessed with the EuroQoL 5-Dimension 5-Level (EQ-5D-5L) scale and the World Health Organization Quality-of-Life Scale (WHOQOL-BREF), respectively. After recruitment into the study, the patients were followed up for 6 months. Routine treatment as per institutional norms was given during this period. The primary caregiver was contacted via telephone monthly for data collection on economic burden. After the 6 months, the participants entered into the next phase (ie, phase 2).

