Parallelly, during phase 1, the PCC intervention model was developed. The rationale behind developing the care model was to provide basic information about DMD and treatment options to the patients and their parents or caregivers so that they could participate effectively in the process of obtaining comprehensive care in a resource-limited setting. The intervention includes information about the disease, an instructional booklet, and a workbook to encourage compliance. This study also includes a teleconsultation with pediatric neurologist and the rehabilitation team. The sessions are designed to facilitate caregivers in decision-making through active participation in every stage of the disease. This set of interventions are collectively referred to as the Comprehensive DMD-Telecare Model.

Phase 2 is the interventional phase of the study, which commences once the patient has completed phase 1 (ie, the first 6 months of the study). During phase 2, patients and their parents or caregivers are given a set of interventions developed during phase 1. The patients are followed up prospectively for the subsequent 6 months (Figure 1), and data on economic burden are recorded telephonically on monthly basis. Children are visiting the health facility just twice during the follow-up period (ie, at the beginning and at the end of phase 2). This reduced the number of in-person visits the patients had to make to the health facility.

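### The out-of-pocket cost comparison does not separate one-off diagnosis and first work-up costs from recurring costs, and with phase 1 always first such costs can load only on the control phase

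*Protocol article*

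**What the plan says.** All references are to the protocol article.

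- **Outcome.** The study outcomes textbox makes the change in mean OOP with and without the intervention a primary outcome measure. The same families are compared, and phase 1 always precedes phase 2 (Study Design).
- **Cost components.** Data Collection says the economic data cover "patient-level expenses incurred on diagnosis and treatment related to DMD". It then defines direct cost: "Expenditure on the diagnosis, drugs or consumables, hospitalization, user fee, or procedure fee is considered direct health care expenditure". Neither this section nor Data Management and Analysis gives a rule that separates one-off from recurring items.
- **Who enters.** Study Design: "Participants (previously diagnosed and under follow-up as well as new patients) were recruited prospectively".
- **What routine care contains.** The routine management textbox lists confirmation of the diagnosis and a baseline work-up ("cardiac, respiratory assessment, spine, bone health, and endocrine" evaluation), along with three-monthly check-ups.
- **When costs are collected.** Data Collection: "Further, after the initiation of phase 1, these caregivers are contacted again prospectively to assess the economic burdens they face". Study Design adds that the enrolment interview also asks about the financial burden of the disease; no recall period is given.
- **Whose income loss counts.** Data Collection: "Wage or income loss by the accompanying caregivers during the period of treatment is considered an indirect expenditure". Data Management and Analysis refers to wage loss of the caregivers without that restriction.
- **Visits in phase 2.** Study Design says children attend "just twice during the follow-up period (ie, at the beginning and at the end of phase 2").

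**The concern.** One cost definition serves two aims. The introduction sets out both an estimate of the economic burden on families and a comparison of the intervention with routine care. Diagnosis cost belongs in the first. In a within-family before-after contrast it does not, because a child is diagnosed and first worked up once, and the planned order puts that at or before the start of phase 1. Whatever part is captured raises the phase 1 mean with no counterpart in phase 2, and the drop that follows would be read as a saving from the intervention.

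There are two routes into the phase 1 total. A new patient's baseline evaluation may be done and paid for after enrolment, or earlier diagnosis cost may be recalled at the enrolment interview and booked to phase 1. The article closes neither route. Since the result is meant to guide policy, an avoidable artefact in a primary outcome should be removed.

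**Working it through.** **The plan's own figure.** The only sample size is for patient quality of life: difference 0.1, SD 0.2, 80% power, 5% significance (taken as two-sided). n per phase = 2 × (1.960 + 0.842)² × 0.2² / 0.1² = 62.8, so 63; with 10% dropout, 63 / 0.9 = 70. Both stated figures reproduce. They do not bear on OOP, for which no effect size or sample size is given.

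**Spurious change under a null intervention.** Set recurring six-month OOP in phase 1 to 1, and let

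- s = share of the compared families whose one-off cost is counted in phase 1,
- D = that cost as a multiple of recurring six-month OOP,
- g = growth in recurring cost from phase 1 to phase 2 caused by progression.

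Phase 1 mean = 1 + sD and phase 2 mean = 1 + g, so the apparent change is (1 + g) / (1 + sD) − 1. The article gives none of s, D or g. The values below are assumptions, chosen to show the range.

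| s | D | sD | g = 0 | g = 10% | g = 20% |
|---|---|---|---|---|---|
| 0 | any | 0 | 0% | +10% | +20% |
| 10% | 0.5 | 0.05 | −4.8% | +4.8% | +14.3% |
| 10% | 1 | 0.10 | −9.1% | 0% | +9.1% |
| 25% | 1 | 0.25 | −20.0% | −12.0% | −4.0% |
| 50% | 2 | 1.00 | −50.0% | −45.0% | −40.0% |

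Example: s = 25%, D = 1, g = 10% gives 1.10 / 1.25 − 1 = −12.0%. The sign turns when g exceeds sD. If one-off costs are left out of both phases, sD = 0 and the apparent change is simply g.

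**The month-6 visit.** Routine visits are every three months, and the start of phase 2 coincides with the end of phase 1. Planned visits at months 0, 3, 6 and 12 split as follows:

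- month 6 in phase 1: months 0, 3, 6 against 12, which is 3 versus 1;
- month 6 in phase 2: months 0, 3 against 6, 12, which is 2 versus 2;
- month 6 in phase 1 and the enrolment visit not counted: months 3, 6 against 12, which is 2 versus 1.

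Transport, food and wage loss follow the chosen split. The sample size section and the outcomes textbox give windows of 0-6 and 7-12 months, but attach them to quality of life; the OOP item carries no window. Applying them to OOP puts month 6 in phase 1.

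**The case against.** The strongest reply is that little diagnosis cost may ever reach the phase 1 total. Genetic or biopsy confirmation is an inclusion criterion, so confirmatory testing mostly precedes enrolment, and OOP is collected prospectively once phase 1 has started. A cost incurred before the window and not booked to it causes no bias. This stands for the confirmatory test. It does not cover a baseline evaluation done after enrolment, or cost recalled at the enrolment interview.

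Second, the introduction says the burden rises markedly with progression, and the Results say disease stages shifted quickly. That pushes phase 2 cost up. It stands as a limit on the net direction, but two opposing influences of unknown size cannot be relied on to cancel, and one of them can be removed by coding.

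Third, the word diagnosis may cover recurring investigations, and the first work-up is not named in the cost definition. This stands; the link rests on reading the cost list beside the routine management textbox.

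Fourth, the article admits that it has no control group and that conditions may differ over time. That general caveat does not address a specific feature of the outcome definition.

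A reader might also infer that costs added by telecare are left out of phase 2, because the non-health list reads "Transportation, boarding, loading, and food are taken as direct" non-health items and income loss is tied to accompanying caregivers. The documents do not support this firmly. The analysis section counts caregivers' wage loss without that limit, the interview schedule is not shown, and a smartphone and internet access are entry requirements, so the added cost may be small. Nor is the month-6 booking wholly open, since phase windows exist. Fewer visits in phase 2 are also the purpose of the intervention; only the placing of the shared visit is a coding matter.

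**Conclusion.** The point holds in limited form. A primary before-after outcome includes diagnosis expenditure without separating one-off from recurring cost, in a design that enrols new patients and fixes the phase order. Any one-off cost that is captured therefore biases the comparison towards a cheaper phase 2.

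The size cannot be derived from the article. It is zero if no such cost enters the phase 1 total. The negative figures in the table show only what follows if the assumed shares and multiples apply; they are not estimates for this study.

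It is tempting to conclude that phase 2 will look cheaper even if the intervention does nothing. The article does not support that: the net sign depends on s, D and g, and progression alone could make phase 2 look dearer. This is a change that should be made, not a fault that invalidates the study.

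**What to change.** Settle the following before the phase totals are compared. The Results report that data are still being entered and cleaned and that no impact data are available.

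1. Base the phase 1 versus phase 2 contrast on recurring OOP only. Exclude diagnosis and first work-up cost from both phases, and any cost incurred before enrolment. Keep repeated monitoring tests, which are recurring.
2. Report the excluded costs separately as part of the burden estimate, where they belong.
3. Repeat the contrast in previously diagnosed patients only.
4. Apply the 0-6 and 7-12 month windows to OOP so that the shared month-6 visit is booked by one rule, and state whether the enrolment visit is counted.
5. Use the analysis section's wording, wage loss of the caregivers, in both phases. If family costs of telecare were not asked about, state this as a limitation; the Results say phase 2 has ended, so the question can no longer be added to the monthly calls.

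The cost is a little recoding and one extra analysis. The apparent saving may be smaller. Growth from progression remains in the contrast, and this fix does not remove it.
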